## Abstract

**Background:** This will be a before-and-after study nested within a randomized clinical trial. Its objective will be to analyze the effectiveness of a teleconsultation and validate a questionnaire for performing teletriage in dental urgency/emergency situations in children aged 3 to 13, whose parents will have signed a free and informed consent form, and who have had full access to the internet.

**Methods:** The Questionnaire for Teletriage of Emergencies and Urgencies in Pediatric Dentistry (QuesT-Odontoped)—will be validated by applying it to 140 randomized child parents/guardians. After validation, another 260 children seeking emergency dental care in the municipality of Carangola, Minas Gerais, Brazil, will receive a remote consultation, be randomized, and then allocated into two groups: G1, teleconsultation, and G2, teleconsultation and face-to-face consultation (immediately after the former) with a blinded evaluator, involving anamnesis and conventional clinical examination. The G2 sample will be used in the before-after study. Both groups will be followed-up for 7 and 14 days using pain and quality-of-life scales, applied at baseline and after each follow-up period. Clinical follow-up will be carried out after 12 and 24 months to assess the outcome of the tooth that had been indicated for treatment in the teletriage. The Mann-Whitney test will be used to assess pain; Student’s t test or the Mann-Whitney test will be used to assess quality of life and the number of missing teeth after 24 months; and Poisson’s regression analysis will be used to assess the influence of other variables. The significance level will be set at 5%.

**Conclusions:** In conclusion, this study expects to confirm the hypothesis that remote urgency consultation (teletriage), through a validated questionnaire, will be able to define the planning of the clinical situation, reducing the chance of displacements and progression of infection, helping to eliminate patient pain and discomfort.

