## Protocol

### Ethics statement

The design of this study (both before-and-after study as well as the randomized clinical trial) was approved by the Research Ethics Committee, School of Dentistry, University of São Paulo (approval no. 46974821.9.0000.0075), on June 1st, 2021. It was also submitted to
*The Brazilian Clinical Trials Registry*, code
RBR-523hrsx. The research protocol was written following SPIRIT
*(Standard Protocol Items: Recommendations for Interventional Trials)* guidelines.
^
30
^

The study will be divided into the following stages: (1) questionnaire validation, (2) randomized clinical trial, and (3) before-and-after study, each with their own methodology.

*Team and participants*

The allocation sequence was generated by an external professional (Dentist, PhD);

The participants enrollment and their assignment to interventions will be carried out by the main researcher ([name]).

*Questionnaire validation*

The inclusion of the research participants in this stage will be made upon a digital acceptance of a free and informed digital consent form (FICF), which will be digitally signed by the person in charge of the child (parents/guardians) and uploaded through a digital link, for this remote part of the study. This form presents the research objectives clearly, as well as the guidelines that will be provided to patients. Permission to disclose data will be part of this document, and shall ensure confidentiality of participant identity. All the participants will be informed that their participation in the study is voluntary and the participants will be informed that their anonymised data will be published.

*Before-and-after study nested within a randomized clinical trial*

For this stage, inclusion of participants in the study groups will also take place upon a digital acceptance of a free and informed digital consent form (FICF), uploaded through a digital link, and parents or guardians must mark the tick – box to consent for the remote part of the study, on behalf of the child. The parents/guardians of participants assigned to the face-to-face consultation group (G2) will also be required to sign a FICF.

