**Figure 2. f2:**
[figure not shown]
Validation of the questionnaire applied in the study.

*Before-and-after study nested within a randomized clinical trial*

The present research project will consist of a randomized, controlled, noninferiority, and blinded (examiners) clinical study, with 260 children aged 3 to 13 years in dental urgency situations. All of the participants investigated will be users of Basic Health Units, hospitals or dental clinics, residing in the municipality of Carangola, MG, Brazil. A link providing access to the Telehealth and Teledentistry Center from the University of São Paulo School of Dentistry (Nutes/FOUSP) platform will be sent to each patient after said patient makes the first contact through

*WhatsApp*
, a messaging app. All patients will be previously evaluated by a previously trained researcher in a teleconsultation (“before”), and then randomized and divided into two groups: G1, comprising 130 patients seen via a teleconsultation, and G2, comprising 130 patients seen via a teleconsultation and also in person (
Figure 3). The face-to-face evaluation (“after”) will be performed by two researchers who will be blinded to the result of the teleconsultation, who will perform anamnesis and clinical examination using a specific dental record, and who will answer whether or not the patient’s case is an urgent situation at the end of the evaluation. The dental condition motivating inclusion of the patient in the study will be treated by the researcher, and any other patient needs will be seen to by referring them to the health unit where they were registered.

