### Assignment

*Questionnaire validation*

The questionnaire will be applied to 140 participants, and reapplied to 14 randomized participants. Randomization, in blocks of four participants, will be performed using statistical software (MedCalc
^®^ 15.11, MedCalc Software, Ostend, Belgium), and the sequence generated will be distributed in sealed brown envelopes.

*Before-and-after study nested within a randomized clinical trial*

Randomization, in blocks of four patients, to assign them to one of the treatment groups, will be performed using statistical software (MedCalc
^®^ 15.11, MedCalc Software, Ostend, Belgium), and the sequence generated will be distributed in sealed brown envelopes. The envelopes must be opened immediately after the start of the teleconsultation.

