### Interventions

The synchronous teletriage will be carried out using the teleconsultation-dedicated
NuTes-FOUSP platform that complies with the LGPD, as well as a questionnaire containing objective questions to ascertain whether or not the situation in question is a case of a dental urgency. The time required to apply the questionnaire will depend on how long it takes to obtain the answers from the patients’ parents/guardians.

In the clinical stage of the study, the time of the face-to-face dental consultation, to be performed immediately after the synchronous consultation shall not exceed one hour.

The clinical situations listed below will be considered dental urgencies (ADA, 2020)
^
2
^:
•irreversible pulpitis;•pericoronitis;•abscess or localized bacterial infection, resulting in localized pain and swelling;•tooth fracture, resulting in pain or causing soft tissue trauma.•dental trauma, involving avulsion and/or luxation;•a missing or fractured restoration, or one causing gingival irritation and requiring a provisional restoration;•extensive caries or a defective restoration that is causing pain;•pain that requires replacing the provisional filling of an endodontic access opening;•perforated or ulcerated oral mucosa, requiring trimming or adjustment of a wire or orthodontic appliance.

The clinical situations listed below will not be considered dental urgencies:
•initial or follow-up dental examination;•routine radiography;•dental prophylaxis;•routine periodontal therapy;•orthodontic procedure other than that needed to treat an acute problem (e.g., pain, infection, trauma);•extraction of an asymptomatic tooth;•restorative dentistry procedure, including treatment of an asymptomatic carious lesion;•aesthetic dental procedure

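### The protocol gives two incompatible times for opening the trial envelopes; one reveals the group before the teletriage decision is complete

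*Protocol article*

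**What the plan says.** The article places the trial's randomisation step in three sections.

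- **Assignment**, trial stage: "The envelopes must be opened immediately after the start of the teleconsultation".
- **Research design**, trial stage: "All patients will be previously evaluated by a previously trained researcher in a teleconsultation", labelled the before assessment, "and then randomized and divided into two groups".
- **Abstract**, Methods: the children "will receive a remote consultation, be randomized, and then allocated into two groups".

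On roles, the team description under the Ethics statement says: "The participants enrollment and their assignment to interventions will be carried out by the main researcher". Research design gives the teleconsultation to a trained researcher and does not say whether this is the same person. The only blinding described is that of the face-to-face assessment, which "will be performed by two researchers who will be blinded to the result of the teleconsultation". Under Interventions, the remote call uses "a questionnaire containing objective questions to ascertain whether or not the situation in question is a case of a dental urgency".

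**The concern.** Two primary outcomes rest on what is recorded around the time of the call.

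- **Before-and-after study.** The primary outcome is any change in the urgent/elective decision after the in-person visit. The remote decision is its first half, and only G2 contributes. An examiner who knows that a colleague will see the child straight afterwards may triage more or less cautiously than one whose decision stands alone. The change frequency would then describe teletriage with a known back-up. The article's stated hypothesis is about what the remote consultation can determine.
- **Randomised trial.** The primary outcome is change in Wong-Baker score from baseline to 7 and 14 days. If baseline is scored after the group is known, the reference value could be influenced differently in the two arms.

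**Working it through.** No figure in the plan is at issue, so the check sets the sections side by side.

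**Step 1: can both orders hold?** The sequence is generated beforehand by an external professional, so for each child the effective moment of randomisation is the opening of the envelope. Assignment puts this just after the call begins. The Abstract and Research design put it after the remote evaluation. An evaluation made in the call cannot be complete just after the call has begun, so the two orders are incompatible. The Research design section also describes envelope opening around the time of the call for the questionnaire validation stage. That is a separate stage and does not settle the order for the trial.

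**Step 2: what is exposed under each order?**

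| Item | Abstract and Research design order | Assignment order |
|---|---|---|
| Remote urgent/elective decision | complete before the group is revealed | completed after the group is revealed |
| Baseline pain and quality of life | before, if taken in the call | after, if taken in the call following opening |
| Tooth to be followed for 12 and 24 months | identified before, if settled in the teletriage | identified after, if settled in the teletriage |

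The first row follows from the text. The other two are conditional, because the article does not say when in the process the scales are applied or the tooth is fixed.

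**Step 3: does anything keep the group from the tele-examiner?** Enrolment and assignment belong to the main researcher. Nobody is named as opening the envelope. No text separates that person from the tele-examiner, and no text says that they are the same. The blinding covers the in-person evaluators, and what is hidden from them is the teleconsultation result.

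**Step 4: how many decisions are exposed?** Under the Abstract and Research design order, 0 of the 130 decisions in G2. Under the Assignment order, up to 130 of 130, if the opener is the tele-examiner or informs that person. This range counts decisions made with the group known. It does not measure bias.

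**The case against.** Two places put evaluation first and one sentence does not, so the Assignment sentence may be a drafting slip that the site ignores. That is possible. However, it is worded as an obligation and stands in the section where staff would look for the procedure.

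There are also partial safeguards. The questionnaire uses objective questions put to parents or guardians, and the article lists which conditions count as urgent, so discretion is narrowed. Blinding of the in-person evaluators protects the second half of the change outcome. The sequence comes from an external professional. All of this stands and limits the likely harm, but none of it conceals the group while the remote decision is being made.

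Three stronger readings are tempting, and the documents do not support them.

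- **That the tele-examiner knows the group for every child.** This needs the Assignment order to govern and the opener to be, or inform, the tele-examiner. The article states neither.
- **That baseline scores and the index tooth are post-allocation data.** The timing of the scales and of the choice of tooth relative to envelope opening is not given.
- **That blocks of four make this worse.** Of the 6 possible block orders (24 positions), the group is forced by earlier allocations in 6 + 2 = 8, or 33.3%. That measures the predictability of the next allocation. It has no bearing on a decision made with the envelope already open. Fixed blocks contradict nothing in the article, and no route to selective enrolment is shown. Envelope numbering is detail that an article can leave to the full protocol.

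**Conclusion.** The contradiction on timing is explicit and unresolved, and it has to be reconciled. The consequence is conditional. If the Assignment order is followed, the group is revealed before the remote decision is complete. If the tele-examiner learns it, the first half of the before-and-after primary outcome is open to influence. If baseline scales are taken in the call after opening, so is the reference for the trial's primary outcome.

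The direction and size of any bias cannot be derived from the documents. The analysis could not repair it afterwards: only G2 has the in-person comparison, so no G2 decision made without knowledge of the group would be available to replace one made with it.

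**What to change.** Amend the Assignment section to match the Abstract and Research design. The envelope is opened only after consent, eligibility, baseline Wong-Baker and quality-of-life scores, the index tooth and the urgent/elective decision have been recorded and locked.

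The cost is small. Opening moves to later in the same call, and staff need a way to lock the listed entries first. The sample size does not change. The Study status section reports the questionnaire still in validation, and the Abstract places the 260 trial children after validation, so the change may come before most or all trial allocations. If any child has already been randomised, document which order was used.

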### Training of examiners/researchers

The examiners/researchers (authors on the paper and two dental practitioners based at the clinics) will be trained by the author responsible for the project ([name]) to carry out the research prior to the first stage. This will involve a four hour training program for urgency situations of dental origin in children, and a 4-hour calibration program for questionnaire application.

Prior to the beginning of the study, the researcher will explain the study and how teledentistry will be used within the Family Health Units to the entire team.

### Interventions

The synchronous teletriage will be carried out using the teleconsultation-dedicated
NuTes-FOUSP platform that complies with the LGPD, as well as a questionnaire containing objective questions to ascertain whether or not the situation in question is a case of a dental urgency. The time required to apply the questionnaire will depend on how long it takes to obtain the answers from the patients’ parents/guardians.

In the clinical stage of the study, the time of the face-to-face dental consultation, to be performed immediately after the synchronous consultation shall not exceed one hour.

The clinical situations listed below will be considered dental urgencies (ADA, 2020)
^
2
^:
•irreversible pulpitis;•pericoronitis;•abscess or localized bacterial infection, resulting in localized pain and swelling;•tooth fracture, resulting in pain or causing soft tissue trauma.•dental trauma, involving avulsion and/or luxation;•a missing or fractured restoration, or one causing gingival irritation and requiring a provisional restoration;•extensive caries or a defective restoration that is causing pain;•pain that requires replacing the provisional filling of an endodontic access opening;•perforated or ulcerated oral mucosa, requiring trimming or adjustment of a wire or orthodontic appliance.

The clinical situations listed below will not be considered dental urgencies:
•initial or follow-up dental examination;•routine radiography;•dental prophylaxis;•routine periodontal therapy;•orthodontic procedure other than that needed to treat an acute problem (e.g., pain, infection, trauma);•extraction of an asymptomatic tooth;•restorative dentistry procedure, including treatment of an asymptomatic carious lesion;•aesthetic dental procedure

### Complications

*Questionnaire validation*

The risks involved in this study are those inherent in virtual environments, electronic media, or non-face-to-face activities, considering the limitations of the technologies used or those of researchers in ensuring data confidentiality and preventing data violation.

*Before-and-after study nested within a randomized clinical trial*

In addition to the risks mentioned above, there are other risks inherent in any pediatric dental treatment, including those related to the possible failure of the proposed dental treatment. Additional risks are those related to data collection, such as possible discomfort felt during the remote and/or face-to-face consultation, during the assessment, examination, and therapeutic procedures themselves, and possible annoyance and/or emotional or social stress occasionally felt by the patient and/or by parent/guardian when answering questions related to the child’s health.

To reduce these risks, the procedures will be monitored by the researcher, who will be prepared to provide all the assistance needed. In the event of personal injury caused directly by any procedure or treatment proposed in this study, the child will be entitled to free dental treatment.

### Data collection

The data will be collected at different timepoints, as shown in
Table 1.

**Table 1. T1:** Data collection. G1, teleconsultation; G2, teleconsultation plus face-to-face consultation.

	Time +/ -	Timepoint	Research actions
Training of examiners/researchers	8 hours	t-1	The examiners/researchers will be trained to carry out the study, including a 4-hour training program for urgencies of dental origin in children, and a 4-hour calibration program for questionnaire application.
Inclusion criteria - Quest - Odontoped	12 months	0	The parents/guardians of children with dental pain, who seek care at the University of São Paulo School of Dentistry, or at the University of São Paulo Health Superintendence (SAU), will receive the contact information for one of the researchers, complete with a telephone number, and information on the requirements for having a remote consultation.
Inclusion criteria (test and control groups) - Carangola, MG, Brazil	12 months	0	When arriving at a Basic Health Unit, a hospital or a dental clinic outside opening hours, the parents/guardians of children with dental pain will find a poster outside containing the contact information for one of the researchers, complete with a telephone number, the number of the ethics committee approval report, and the requirements for having a remote consultation.
Follow-up	1 week and 2 weeks	T1	Patients in G1 and G2 will be followed-up for 7 and 14 days using specific instruments to assess the absence or presence of pain (Wong-Baker scale), and the quality of life according to the child's age.
Follow-up	12 months and 24 months	T2	In the event of urgencies involving teeth, a 12- and 24-month follow-up of the tooth reported in the teletriage will be carried out. The clinical criteria used to determine treatment success will be no fistula or exudate, no abscess, no painful symptoms, and no pathological mobility.
Close-out	24 months	tx	Analysis and dissemination of research results.

### Sample size

*Sample for questionnaire validation*

The guidelines of the European Statistical System stipulate that the development and validation of instruments must follow five steps: (1) conceptualization, (2) questionnaire design, (3) questionnaire testing, (4) revision, and (5) data collection.
^
34
^ Considering that the questionnaire conceptualization and design have already been completed, our considerations will begin from the questionnaire testing step. The first step involved in instrument testing is evaluation by a panel of experts (content validation). There is a controversy in the literature regarding the recommended size for this panel, ranging from five to twenty members,
^
35
^
^,^
^
36
^ depending on their experience and qualifications. Subsequently, data collection will be carried out by applying the questionnaire (criterion validity). To this end, a sample size of at least 10 participants is recommended for each item
^
37
^; therefore, the minimum sample size of the present study will be 140 subjects. In order for the instrument to be considered reliable (test and retest), it must be able to produce similar results when applied to the same individual at different times, and by different interviewers. For this purpose, a sample size corresponding to 10% of the total “N” (i.e., 14 patients in the current version of the questionnaire) should be used.

*Sample size calculation for the RCT*

Primary outcome: the presence of dental pain in children and adolescents, considering independent samples (in this case, there is no pairing of individuals, and the interventions will be assigned to different individuals). The possibility of dropouts during the follow-up period was taken into account.

In performing the sample size calculation for independent samples, the proportion of dental pain observed in children and adolescents will be considered as 32.7%,
^
38
^ and the minimum, clinically relevant proportion difference will be 15%. Thus, considering a two-tailed test, a significance level of 0.05, and a power of 0.80, the calculation will yield a total number of 236 patients. Owing to the possibility of participant dropout during the follow-up period, 10% of this number will be added to the final sample, bringing the total number of patients required per experimental group to 130 (G Power, version 3.1.9.4).

*Sample size calculation for the before-and-after study*

Before-and-after studies are considered observational studies, and use a preliminary diagnostic test to decide whether or not to treat a series of examined patients. These patients are submitted to another diagnostic method, and the treatment decision can then be revised. Since this before-and-after study is nested within a randomized controlled trial (RCT), the sample size calculation will take into account the primary outcome of the RCT and the two experimental groups. However, only the group evaluated using both methods (teletriage + face-to-face consultation) will be eligible for this study. Therefore, the before-and-after study sample will consist of 130 patients.

*Outcomes*

Primary outcome: the presence of dental pain in children and adolescents, considering independent samples.

Secondary outcome: quality of life (questionnaires according to age group) and tooth loss.

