### Inclusion and exclusion criteria

The inclusion criteria will be the same for the two stages of patient selection in the study.

*Inclusion criteria*
a)children aged 3 to 13 years, with dental pain, whose parents seek urgent care at the Dental School of the University of São Paulo in São Paulo, or at the public network in the city of Carangola, in the state of Minas Gerais.b)patients with a sufficiently good internet connection to allow a synchronous consultation.

*Exclusion criteria*

The exclusion criteria will be the same for the two stages of patient selection of the study:
a)patients who fail to attend the face-to-face consultation, when assigned to G2;b)patients with internet access difficulties.

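### The stated inputs do not give 236 patients: a two-sided comparison of proportions needs 262 or 334, depending on a direction that is not stated

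*Protocol article*

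**What the plan says.** The section on sample size for the RCT in the Protocol article names the presence of dental pain in two independent groups as the primary outcome. For the reference rate it says that "the proportion of dental pain observed in children and adolescents will be considered as 32.7" per cent, and for the effect that "the minimum, clinically relevant proportion difference will be 15" per cent. The operating characteristics and the result are given together: "considering a two-tailed test, a significance level of 0.05, and a power of 0.80, the calculation will yield a total number of 236 patients". For dropout, "10% of this number will be added to the final sample", which leads to 130 per group. G Power 3.1.9.4 is cited, but not the test chosen in it.

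The Research design section gives the same allocation: "G1, comprising 130 patients seen via a teleconsultation, and G2, comprising 130 patients seen via a teleconsultation and also in person". It also labels the trial noninferiority. The Data analysis section defines the primary outcome as change in Wong-Baker pain score at 7 and 14 days and compares the groups with a Mann-Whitney test. The inclusion criteria admit "children aged 3 to 13 years, with dental pain".

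**The concern.** The article prints every input that a two-proportion calculation needs except the direction of the difference, so its result can be checked. If 236 does not follow from those inputs, the 80% power is not a property of the design. A reader who meets a null result would then take more reassurance from it than the trial can give.

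Two further features make the power figure hard to interpret. A 15-point difference from 32.7% has a larger variance going up than going down, so the unstated direction changes the answer substantially. And 32.7% is described as the proportion of dental pain in children and adolescents, whereas every child enrolled has pain at entry and is assessed one and two weeks later.

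**Working it through.** **Inputs (Sample size calculation for the RCT).** p1 = 0.327; difference 0.15, so p2 = 0.177 or 0.477; two-sided α = 0.05 (z = 1.960); power 0.80 (z = 0.842); 1:1 allocation; stated total 236, or 118 per group; enrolled 260, or 130 per group.

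**Attempt to reproduce 236.** Pooled-variance two-proportion formula, with p̄ = (p1 + p2)/2:

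n per group = [1.960·√(2p̄(1−p̄)) + 0.842·√(p1(1−p1) + p2(1−p2))]² / (p1 − p2)²

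- Down to 17.7%: p̄ = 0.252; (1.960·√0.37699 + 0.842·√0.36574)² / 0.0225 = (1.2034 + 0.5090)² / 0.0225 = 130.3, so 131 per group, **262** in total.
- Up to 47.7%: p̄ = 0.402; (1.960·√0.48079 + 0.842·√0.46954)² / 0.0225 = (1.3590 + 0.5767)² / 0.0225 = 166.5, so 167 per group, **334** in total.

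Other two-sided methods do not return 236 either:

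| Method | Down to 17.7% | Up to 47.7% |
|---|---|---|
| Pooled | 262 | 334 |
| Unpooled | 256 | 328 |
| Arcsine | 258 | 334 |
| Continuity-corrected | 288 | 360 |

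Two-sided Fisher exact (down) has 71.7% power at 118 per group and needs more than 140 per group. Rates centred on 32.7% give 306 in total. Reading the 15% as a relative change gives over 2,700.

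**Dropout step.** 236 × 1.10 = 259.6, which matches 260. If 10% of 260 are lost, 260 × 0.90 = 234 remain, or 117 per group.

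**Power actually available.** Power = Φ[(0.15 − 1.960·s0)/s1], with s0 = √(2p̄(1−p̄)/n) and s1 = √((p1(1−p1) + p2(1−p2))/n). For n = 117:

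- Down: (0.15 − 1.960 × 0.05676)/0.05591 = 0.693, so 75.6%.
- Up: (0.15 − 1.960 × 0.06410)/0.06335 = 0.385, so 65.0%.

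| Analysed per group | 32.7% v 17.7% | 32.7% v 47.7% |
|---|---|---|
| 117 (260 less 10%) | 75.6% | 65.0% |
| 118 (the stated 236) | 75.9% | 65.3% |
| 130 (no loss) | 79.9% | 69.6% |

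**Difference detectable with 80% power at 117 per group.** Solving the same expression from 32.7% gives about 15.7 points down or 18.0 points up.

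**Sensitivity to the reference rate.** The documents give no 7- or 14-day pain rate, so the range here is an assumption. For a 15-point fall at 117 per group, power is 94% from a base of 20%, 79% from 30%, 69% from 40%, 64% from 50% and 63% from 60%.

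**Noninferiority reading.** Suppose the 15 points are a margin and both arms have 32.7%: n = (z_α + 0.842)² × 2 × 0.327 × 0.673 / 0.0225. One-sided 0.025 gives 154 per group (308). One-sided 0.05 gives 121 per group (242).

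**The case against.** The strongest reply is that the shortfall is small. The planned sample is 260, and with full retention it has 79.9% power for a fall to 17.7%, in effect the stated figure. It would be too strong to say that the planned sample as such gives 76%: that figure describes the 234 to 236 analysed after the planned loss. This stands as a limit on the point. But the 10% was added to protect the 80% against dropout, and here it is used up before anyone is lost. In the upward direction, 260 falls short even with full retention.

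A reader might infer that the 65% figure is the one that applies when teleconsultation is worse. The article does not support this, because it assigns 32.7% to neither arm. With teleconsultation at 32.7% and the comparison group at 17.7%, teleconsultation being worse is the 76% case. Both directions must be shown.

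A reader might also look for the cause. A second proportion of 0.17 gives 117.7, so 118 per group, exactly 236. One-sided 0.05 calculations come close (continuity-corrected 232, Fisher exact about 230). Both are fits after the fact; neither is documented, and the one-sided route contradicts the stated two-tailed test. The noninferiority reading at one-sided 0.05 (242) has the same conflict, and at one-sided 0.025 it needs 308.

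Multiplying by 1.10 instead of dividing by 0.90 changes the enrolled total by only 2 to 3 patients (260 against 262.2, rounded up to 263) and is openly described. It is not part of the point. Whether 32.7% suits follow-up depends partly on a cited source that is not available here, so the claim is only that the article does not show it.

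**Conclusion.** The point holds. The printed inputs and the printed 236 are incompatible under every two-sided method tried: the standard calculation needs 262 or 334 analysable children. At the 234 expected after the planned loss, power is about 76% for a fall to 17.7% and 65% for a rise to 47.7%, against the stated 80%.

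This rests on reading the 15% as percentage points, on 1:1 allocation and on a two-sided 5% comparison of the proportions with pain. The non-reproduction is certain; its cause is not known. The figures describe a comparison of proportions. They are not the power of the Mann-Whitney test on pain-score change in the Data analysis section, nor of a noninferiority test. So the article states no power for the analysis it plans, and correcting the arithmetic alone would not supply it.

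**What to change.** Keep 260 and revise the sample size section:

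1. Reconcile the total, the sidedness and the direction of the difference, and say which arm the 32.7% refers to.
2. Restate the claim for 117 evaluable per group as about 76% power for 32.7% against 17.7%, or 65% for 32.7% against 47.7%. Equivalently, claim 80% power for about 15.7 points down or 18.0 points up.
3. Say that these figures apply to the proportion with pain, and match the power statement to the primary test that is kept. If that is the Mann-Whitney comparison of score change, give power for it. If noninferiority is kept, give power for the margin test.
4. Show power over an assumed range of 7- and 14-day pain rates. Base rates of 20% to 60% give 94% to 63% for a 15-point fall.

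The before-and-after study takes its 130 patients from the same calculation, so its justification should be updated alongside. The cost is a set of slightly less favourable stated figures and some rewriting, with no extra patients.
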